### Eligibility criteria

Three groups of parent-child dyads will be recruited: intervention (n = 140), control (n = 70), and outcome reference (n = 70; Table 1).

### Allocation

After recruiting MAM children they will be randomized 1:1 into two groups: Group A and Group B (Table 2). Computer generated randomized sequences will be used to allocate these children into different groups. The randomized sequences will be generated by a study investigator who will not be directly involved in assigning intervention during enrolling the participants to avoid bias. These sequences will be sealed in white opaque sealed envelopes and will be opened in front of the mother or legal guardian once they consent for the child by the study physician.

**Table 2 pone.0296529.t002:** Intervention scheme.

Group			Number	Intervention
Control group Non malnourished children at 1 year ± 1m (WLZ >-1 SD)			70	No nutritional and psychosocial intervention. Only follow-up
Intervention group (n = 140) With WLZ <-2 and ≥-3, and/or MUAC <12.5 and ≥11.5 cm having MAM at 1year ± 1m	Randomization Into two groups	Group A	70	500 kcal/day RUSF daily till WLZ >-1 achieved or for a maximum of 3 months and then SQ-LNS will be provided for up to the end of the study period. Psychosocial stimulation
		Group B	70	500 kcal/d Enhanced WLZ >-1 achieved or for a maximum of 3 months and then E-SQLNS will be provided for up to the end of the study period. Psychosocial stimulation
Outcome Reference group With WHZ <-2 and ≥-3 z-score, and/or MUAC <12.5 and ≥11.5 cm having stable MAM at 3 years ± 2m			70	After completing the baseline assessment, participants will be provided with daily RUSF (Nutriset’s Plumpy’Sup^™^, RUSF) for 2 months and referred to NRU at icddr,b or local facilities if needed.

### Intervention

The trial includes a non-malnourished cohort (n = 70), MAM intervention cohort (n = 140), and MAMs control group (n = 70). Children included in the MAMs intervention cohort will be randomized (1:1) to receive either the locally produced Ready to Use Supplementary Food (RUSF) at 500 Kcal/day, or Enhanced Ready to Use Supplementary Food (E-RUSF) at 500 Kcal/day (Table 2). The intervention will be started within one week of completion of baseline assessment.

### Nutritional supplement

Amongst the several treatment options to manage MAM children, one of the options is to treat these children with RUSF. As per the World Health Organization (WHO), within the Global Nutrition Cluster, discussions centered around a guidance tool known as the "MAM decision tool." This tool involved exploring various treatment options, one of which included providing Ready-to-Use Food for children aged 6 to 59 months experiencing MAM [24] Several other studies also used RUSF in various clinical trials and found significant improvement in health of MAM children [25]. In Bangladesh, previously rice-lentil based RUSF was locally produced and tested for acceptability [26]. Subsequently, these feeds were utilized in a cluster randomized trial conducted in Bangladesh. The trial involved administering these feeds to 6-month-old children over a year, revealing a significant increase in their average length [27]. The Bangladesh RUSF is an energy-dense rice and lentil-based feed, delivering 250 calories per 50-gram serving, with 45–50% of the calories coming from fat and 8–10% from protein. This RUSF is the Standard- will be produced in a hygienic, sterile food processing laboratory at the Mirpur clinic, by an expert clinical nutritionist, using locally available and culturally acceptable ingredients [26].

E-RUSF (Enhanced- Ready to Use Supplementary Feed adjustment for key nutrients, Nutriset-fr) will be offered to the other 1-year-old intervention group. These feeds contain 24 micronutrients (vitamins and minerals) provided at RDA (Recommended Daily Allowance) levels, functional lipids (Long Chain Polyunsaturated Fatty Acids DHA and EPA), sialylated milk oligosaccharides, neural specific antioxidants (zeaxanthin, lutein; crypto-xanthin) and microbiome modulating dietary soluble fiber mix (inulin + FOS) [28–31].

SQ-LNS, Small Quantity Lipid -based Nutrient Supplements (20gm packets per day) also known as Nutri-butter Plus (Nutriset-fr) will be offered to the children who received the local RUSF for the 2-year follow up period [32]. E-SQLNS (SQLNS enhanced with the same micronutrients in E-RUSF) will be offered to those who received the E-RUSF feed.

All enrolled MAM children will take these feeds daily in addition to their regular complementary feeds at home.

### Dietary intervention

Group A: MAM intervention group participants (n = 70) who will be randomized to receive Bangladesh RUSF will receive two packets of that RUSF for consumption providing approximately 500 kcal/day until the child’s weight for length returns to the ‘normal’ range (WLZ >-1), or for a maximum period of 3 months. Once the child’s appetite returns from the high intake drive during rapid catch up to normal intake (which happens when the child reaches their WLZ >-1), they will be provided with daily 1 packet SQLNS (20 gm) for the remainder of the 2-year follow-up.Group B: MAM intervention group participants (n = 70) who will be randomized to receive E-RUSF will be provided with 1 packet daily providing the same number of calories per day as RUSF, until anthropometric recovery (WLZ >—1SD) is achieved, or for a maximum of 3 months. Once anthropometric recovery is achieved these individuals will then receive 1 packet of E-SQLNS (26gm) daily until the end of the 2-year follow-up period.

Data from children who do not reach the expected anthropometric recovery (WLZ >—1SD) after 3 months, will remain in the study as an “Intention to Treat” group. However, they will be referred to the Nutrition Rehabilitation Unit at icddr,b for additional evaluation and management to exclude secondary causes of malnutrition (e.g. Tuberculosis). These children will continue to receive close monitoring with necessary interventions. MAM participants will be followed up for two years to 3 years of age with biological sample collection, anthropometry and neurocognitive assessment at 2 years (22m-26m) and 3 years (34m-38m) of age.

All children will be provided free primary care at the study clinic by designated medical officers and the families will be provided refreshments and will be paid conveyance bills during their visit to study clinic for performing any assessments.

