## Introduction

### Background and rationale

Nutrition is essential at all stages of life, beginning before birth and continuing throughout childhood. During these periods, critical developmental windows facilitate healthy brain development, including their behavioral correlates (particularly cognitive, motor, and socio-emotional skills [1]. In low- and middle-income countries (LMICs), 45% deaths are due to undernutrition, where around 2 billion survivors suffer long-term cognitive and behavioral consequences [2]. While less than half of all children under-five live in LMICs, nearly 66% of all stunted and 75% of all wasted children live in this region. The highest global prevalence of stunting is found in Asia, with 53% of all stunted children, and 70% of all wasted children located in Southern Asia [3, 4], making this region a high priority for intervention. Since 2000, stunting has steadily declined but a high prevalence of wasting persists hindering the achievement of Sustainable Development Goal 2: zero hunger targets by 2030 [5, 6], an important marker for development in this region.

Bangladesh, situated in the Indian subcontinent bordering the Bay of Bengal, is amongst the most densely populated countries globally [7]. Malnutrition is a significant health issue, with approximately one-third of preschool-age Bangladeshi children being stunted (low height-for-age), ≥ one-fifth are underweight (low weight-for-age) and approximately one-tenth are wasted (low weight-for-height) [8–10]. In Bangladesh, approximately 1.8 million children under 5 years of age suffer from Moderate acute malnutrition (MAM) [11–13], diagnosed as weight-for-height (WHZ) or weight for length (WLZ) z-scores between <-2 and ≥-3 of WHO child growth standards and/or mid upper arm circumference (MUAC) <12.5 and ≥11.5 cm [14, 15].

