### Recruitment

Enrollment was initiated on February 7, 2022 and will continue until February 2024.

Study surveillance workers (SWs) conducted a door-to-door census (~ 100,000 households) in Mirpur DNCC wards ward 2, 3 and 5 between January and December 2022. The primary focus of the census was to compile a list of babies aged 11 to 13 months and 34 to 38 months. Verbal consent was obtained to participate in the census. The census identified 5,736 children aged between 11 to 13 months and 2,314 children aged between 34 to 38 months. During the census, if the guardian verbally consented to the study procedure, and the babies met the inclusion and exclusion criteria of the study (Table 1), the SWs proceeded to measure the mid-upper arm circumference (MUAC) of the child. We are inviting mothers of the babies who are within the expected MUAC range to visit the study clinic for further assessment and enrollment.

**Table 1 pone.0296529.t001:** Eligibility criteria.

Intervention group	Control group	Outcome reference group
1 year MAM (n = 140)	1 year well-nourished (n = 70)	3 years MAM (n = 70)
*Inclusion Criteria*:		
Child aged between 1year ± 1m (11m–13m).	Child’s aged between 1 year ± 1m (11m–13m).	Child aged between 3 year ± 2m (34m–38m).
Child’s WLZ/WHZ score is <-2 and ≥-3, and/or MUAC <12.5 and ≥11.5 cm. Child is free from any acute illness.	Child’s WLZ/WHZ score is > -1 SD, Child is free from any acute illness.	Child’s WLZ/WHZ score is <-2 and ≥-3, and/or MUAC <12.5 and ≥11.5 cm. Child is free from any acute illness.
Mother is willing to sign informed consent form.	Mother is willing to sign informed consent form.	Mother is willing to sign informed consent form.
*Exclusion Criteria*:		
Child aged > 13 months or < 11 months.	Child aged > 13 months or < 11 months.	Child aged > 38 months or < 34 months.
Child has any congenital anomaly.	Child has any congenital anomaly.	Child has any congenital anomaly.
Mother is unwilling to sign informed consent form.	Mother is unwilling to sign informed consent form.	Mother is unwilling to sign informed consent form.
Mother unwilling to bring child to the clinic for assessments or to use intervention feeds on child.	Mother unwilling to bring child to the clinic for assessments	Mother unwilling to use the rehabilitation feed on child or the small quantity supplement.

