Final screening for eligibility and study consent will occur at the Mirpur study clinic (S1 File). Because the primary study population is incapable of assenting, due to age 1year ± 1m and 3 years ± 2m, parental permission will be obtained for study participants. The consenting process will be done by a study physician. The consenting process will be tailored to each mother’s literacy level and will involve reviewing the inclusion and exclusion criteria. Comprehension of the study will be assessed using scripted points and open-ended questions. After obtaining consent, the clinical screening team will proceed with anthropometric screening of the child and mother.

Following consent, the clinical screening team will complete a screening form (Supplementary materials 1), capturing the date of visit, sex, date of birth (DOB), weight (in kg), length/ height (in cm), head circumference (in cm), and MUAC (in cm) measurements of the child. The team will calculate the WLZ/WHZ Z-score for the child using the WHO anthropometric calculator. The child’s age will be validated using the EPI vaccination card.

Final enrollment eligibility is based on matching the Z-score and other physical examination findings with the eligibility criteria (Table 1).

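### Children can enter as MAM on MUAC alone, but recovery, the feed switch, weekly monitoring and referral are judged on WLZ > -1 only

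*Protocol article*

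**What the plan says.** **Entry.** The Background defines MAM by "z-scores between <-2 and ≥-3 of WHO child growth standards and/or mid upper arm circumference (MUAC) <12.5 and ≥11.5 cm". Table 1 (Recruitment) uses the same two limbs for the intervention group: "WLZ/WHZ score is <-2 and ≥-3, and/or MUAC <12.5 and ≥11.5 cm". The Abstract and Table 2 repeat the either-or form. Field staff measure MUAC, and the route to the clinic is through it: "We are inviting mothers of the babies who are within the expected MUAC range to visit the study clinic for further assessment and enrollment". The final check adds no further limit: "Final enrollment eligibility is based on matching the Z-score and other physical examination findings with the eligibility criteria (Table 1".

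**Leaving the rehabilitation phase.** Table 2 gives Group A "500 kcal/day RUSF daily till WLZ >-1 achieved or for a maximum of 3 months", and the Abstract says that the earlier of the two events applies. In the Dietary intervention section the Group A switch to SQLNS is linked to normal appetite, "which happens when the child reaches their WLZ >-1), they will be provided with daily 1 packet SQLNS (20 gm". Group B moves to E-SQLNS on the same WLZ threshold. The same section refers children who have not passed WLZ > -1 by 3 months, and the Anthropometric data section ends weekly measurement at WLZ > -1 and continues quarterly. MUAC is among the measures taken but appears in none of these rules.

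**Start of feed.** The Intervention section has feeding begin within a week of the baseline assessment.

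**The concern.** The rule for entering the rehabilitation phase has two limbs and the rule for leaving it has one. A child who came in through MUAC is then judged on a measure that need not have been abnormal at entry. Four things depend on the exit rule:

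- **Feed exposure.** It decides how long the child receives RUSF or E-RUSF, which is the first part of the randomised contrast.
- **The recovery label.** It also decides who joins the non-recovered group that the protocol labels intention-to-treat.
- **Sample timing.** The extra blood and stool samples in the intervention group are tied to anthropometric recovery or to the 3-month point (Blood analytes, Stool collection).
- **Monitoring and referral.** It sets the move from weekly to quarterly anthropometry and the referral at 3 months.

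If recovery means catch-up for some children and only the absence of low WLZ at entry for others, none of these four has a single meaning.

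**Working it through.** The protocol gives no figure to reproduce here, so the check is one of logic, followed by an illustration of frequency.

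**1. The two sets.**

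- Entry as MAM: (-3 ≤ WLZ < -2) or (11.5 ≤ MUAC < 12.5 cm), from the Background and Table 1.
- Recovery: WLZ > -1, from the Abstract, Table 2, Dietary intervention and Anthropometric data.
- Overlap: 11.5 ≤ MUAC < 12.5 cm with WLZ > -1. It is not empty.

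**2. Two constructed children.**

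| Child | WLZ | MUAC (cm) | MAM by Table 1 | Meets recovery rule |
|---|---|---|---|---|
| 1, at randomisation | -0.8 | 12.3 | yes (MUAC) | yes |
| 2, at randomisation | -1.5 | 12.3 | yes (MUAC) | no |
| 2, later | -0.9 | 12.4 | yes (MUAC) | yes |

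Child 1 should start RUSF or E-RUSF within a week of baseline under the Intervention section, yet already meets the rule that ends it. Staff cannot follow both. Child 2 is switched, leaves weekly measurement and falls outside the referral rule while still MAM as defined. The 3-month cap prevents neither case, because the earlier event governs.

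**3. Frequency, on assumptions only.** The documents give no joint distribution of WLZ and MUAC. Under a bivariate normal model with mean WLZ -1.0 to -0.7 (SD 1), mean MUAC 13.5 to 14.1 cm (SD 1) and correlation 0.6 to 0.8:

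- MUAC-only entrants are about 14% to 54% of children eligible under Table 1.
- Those with WLZ > -1 at entry are about 0.2% to 19%. Of 140, that is 140 × 0.002 = 0.3 to 140 × 0.19 = 27, so between none and about 27 children.
- If every entrant is reached through the MUAC range, the share with WLZ > -1 is about 0.7% to 26%.

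Under a similar model (mean WLZ -1.2 to -0.6, SD 1.05; mean MUAC 13.6 cm, SD 1.0; same correlations), a further 12% to 37% of Table 1 eligibles enter on MUAC with WLZ between -2 and -1. These children could follow the path of child 2; how many would is not known.

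**4. Effect on the randomised contrast.** Let a share p of children lose a fraction f of the total contrast. The mean contrast is multiplied by 1 - pf, and the effective sample size by (1 - pf)².

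- The first phase lasts at most 3 of 24 months. If effect is proportional to time on the enhanced feed (an assumption), f is at most 3/24 = 0.125. With p = 0.15: 1 - 0.15 × 0.125 = 0.981, and 0.981² = 0.96. With p = 0.19: 1 - 0.19 × 0.125 = 0.976, and 0.976² = 0.95.
- If the whole effect came from the first phase (f = 1), p = 0.15 gives 0.85² = 0.72.

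**The case against.** The strongest reply is that the exit rule is an operational marker and not an endpoint. Objectives and trial design names executive functions and emotion regulation as the primary outcome, and the secondary outcomes do not include recovery. A reader might infer that the rule inflates a recovery rate and hides a difference between arms, but the protocol declares no such comparison. That part of the objection stands.

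Secondly, the contrast does not end with the first feed. Nutritional supplement describes E-SQLNS as carrying the same added micronutrients as E-RUSF, and it continues against SQLNS to the end of follow-up. A reader might take the 72% figure above as the trial's loss of effective sample size. For the outcomes at 2 and 3 years that would require about two years of E-SQLNS to do nothing, which the documents do not support. This stands too.

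Thirdly, the rule has the same form in both arms, so it does not favour either.

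Fourthly, calling this an unguarded safety gap would go too far. Children who leave weekly measurement still have quarterly anthropometry including MUAC, home visits under the stimulation programme, and free primary care. What they miss is the automatic referral.

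None of this removes the conflict. It is a stated delivery rule, not detail left to an analysis plan, and followed exactly it gives child 1 no defined period on the randomised rehabilitation feed.

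**Conclusion.** The point holds as a contradiction between stated rules. A MUAC-only entrant can satisfy the recovery rule on the day of randomisation, against the stated start of feeding, or can be called recovered while still MAM by the document's own definition. For such children the rehabilitation-feed phase is absent or short, the recovery label and the recovery-timed samples are not comparable with those of WLZ entrants, and the WLZ-based referral does not apply.

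The documents show that this can happen, not that it does. Roughly 0 to 20% with WLZ > -1 at entry rests wholly on assumed distributions, and a share near zero is compatible with them. The cost is confined to the first phase, at most 3 of 24 months. If effect follows time on the enhanced feed, about 95% or more of the effective sample size remains for the later outcomes; if the first phase matters more than its length suggests, the loss is larger. There is no between-arm bias.

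**What to change.** Reconcile the entry passages (Abstract, Background, Table 1, Table 2) with those on recovery, start and end of the rehabilitation feed, monitoring and referral (Abstract, Table 2, Intervention, Dietary intervention, Anthropometric data). State what applies to a child who enters on MUAC with WLZ already above -1, and to one who passes WLZ > -1 with MUAC still in the MAM range. Which clinical rule to adopt is for the investigators.

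From the anthropometry already collected:

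- derive entry route (WLZ, MUAC, both);
- in any summary of recovery, do not count a child with WLZ > -1 at entry as having recovered;
- report days on RUSF or E-RUSF by arm and entry route.

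The cost is a protocol clarification, one derived variable and one table, with no added measurements for the derivation and reporting.

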### Psychosocial stimulation

Standard psychosocial stimulation will be provided to the MAM intervention groups. Psychosocial stimulation will consist of bi-weekly, set stimulation curriculum “REACH-UP”. The Reach Up curriculum is a semi-structured, culturally relevant child-age appropriate curriculum that addresses key components of the “nurturing care framework” to promote optimum development [33]. The developmental tasks will take place within a playful environment rather than a work-focused one. During home visits, health-workers will demonstrate to mothers how to play with home-made toys and books and interact with their children aimed at fostering their growth and development.

Toys will be given to the child to play with and learn from, until the next visit, when a new set of developmentally appropriate toys will be provided. The activities in the curriculum are ordered by difficulty level and the health workers will be trained to choose the level for each child according to their ability to do the activities.

### Assessments

Assessments (neuropsychological, behavioral, nutriome, metabolome, and microbiome) will be conducted at baseline, during anthropometric catchup, at 2 and 3 years.

Age, sex, date-of-birth, demography and socio-economic status, medical history, and feeding history will be collected at the time of enrollment.

### Anthropometric data

Weight, length/height, MUAC, head circumference will be measured using established methods (Supplementary materials).

For the intervention group (n = 140 children with MAM), anthropometric data will be collected at enrollment, weekly during catch up anthropometric recovery (WLZ >-1), and quarterly for the duration of the study until 36 months of age. Head circumference will be measured at enrollment, at 2 and 3 years of age.

Anthropometric data will also be collected from the control group (n = 70 healthy children) at enrollment, then monthly for 3 months, then quarterly for the duration of the study until 36 months of age. Head circumference will be measured at enrollment, at 2 and 3 years of age.

For the 3-year-old MAM control group, anthropometric data will be collected only at enrollment.

### Neuropsychological assessment

Neurodevelopmental assessment data for the control and intervention groups will be collected at enrollment (1year ± 1m), 2years ± 2m, and at 3 years ± 2m. Neurodevelopmental assessment data for the outcome reference group will be collected only at enrollment.

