### Data analysis plan

The study will result in a rich data set consisting of neuropsychological assessments of executive functions and emotion regulation, blood nutriome and metabolome, microbiomes, genetics, nutritional status, age, sex, DOB, demography and SES from family, medical history of these children.

Statistical tests will be conducted to quantify differences in the neurocognitive assessments (e.g. EF, NIRS and EEG responses) between and within the wasted and non-malnourished cohorts, all of whom have varied levels of exposure to adversities (single adversities, composite exposure scores, and income). Three model types will be employed, (a) a t-test for analyzing univariate outcomes, (b) linear mixed models, and (c) structural equation modeling to analyze multivariate outcomes.

T-tests will be conducted with an alpha level of 5% and the distributions of the two samples will be checked for normality, homogeneity of variances and autocorrelation in the residual terms. The False Discovery Rate (FDR) method will be applied to correct for potential multiple comparisons.

Linear mixed effects model will be used to evaluate longitudinal effects with respect to the group differences and the relationship with other earlier biological and/or psychosocial risk factors, particularly focusing on the brain power and functional change in development. Since these measurements are repeated at three time points, mixed models with either random intercept or random slope will be considered.

Structural equation modeling will be used to evaluate multivariate relationships. Model fit will be evaluated using descriptive fit indices such as the Comparative Fit Index (CFI) which work with relatively small sample sizes (Bentler et al, 1990) [50].

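### The t-test cannot adjust for age at testing, although raw scores are taken in four-month windows and the main malnutrition contrasts are not randomised

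*Protocol article*

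**What the plan says.** The Neuropsychological assessment section of the protocol article has the control and intervention groups tested at enrollment (1 year, plus or minus 1 month) and again at "2years ± 2m, and at 3 years ± 2m". The Dietary intervention section gives the same follow-up windows in months: "neurocognitive assessment at 2 years (22m-26m) and 3 years (34m-38m) of age". Both follow-up windows are four months wide; the enrollment window is two.

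The outcome reference group is tested on a different basis: "Neurodevelopmental assessment data for the outcome reference group will be collected only at enrollment". Its eligibility criterion in Table 1 (Recruitment) is "Child aged between 3 year ± 2m (34m–38m"), so its age at testing is its age at entry.

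The Data analysis plan names three model types, beginning with "a) a t-test for analyzing univariate outcomes, (b) linear mixed models"; the third is structural equation modeling. The t-test is set at 5%, with checks on distribution, variance and residuals and a false-discovery-rate correction. None of these concerns age. The Sample size section uses Student's t-test to power well-nourished versus wasted children at 1 and 3 years. The mixed model is introduced with "Since these measurements are repeated at three time points"; the article does not say how time is coded.

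Exact age is available. Date of birth is recorded at screening, and the child's "age will be validated using the EPI vaccination card".

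**The concern.** The Executive functions section says the tasks are meant to capture these skills as they emerge, and the development of executive function and emotion regulation is the primary outcome. Raw scores on such measures can be expected to change with age over months. A shared window limits each child's age, but it does not give two groups the same mean age.

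Randomisation covers only Group A versus Group B. Well-nourished controls and reference children are recruited separately, and the article describes no age matching between groups. The reference group is the most exposed. Its test age depends on when a child is found and enrolled, whereas the followed children's age-3 test age depends on a scheduled visit. With a single assessment, the reference group also gains nothing from repeated-measures modelling.

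At stake is whether a difference labelled as malnutrition, or as treated versus untreated malnutrition at age 3, partly reflects one group being older when tested.

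**Working it through.** **1. The plan's own figure.** The Sample size section gives 51 per group for 80% power, one-tailed 5%. The exact t-test solution for a difference of 0.5 SD is 50.15, rounded up to 51, with power 80.6%. So 51 reproduces with 0.5 SD, the usual medium effect. The printed 2 SD would need only 4 per group. I use 0.5 SD as the planned effect.

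**2. Inputs.**
- From the documents: four-month windows; 51 per group as the minimum and 70 per group enrolled; alpha 5%.
- Assumed, because the documents give neither: raw scores rise 0.05-0.15 SD per month, and the two groups' mean test ages differ by 1 month.

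**3. Bias.** Bias = slope × difference in mean age.
- 0.05 × 1 = 0.05 SD, or 10% of 0.5 SD.
- 0.15 × 1 = 0.15 SD, or 30% of 0.5 SD.

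**4. Error rate with no true group effect.** The t statistic is noncentral, with noncentrality = bias × √(n/2) and 2n − 2 degrees of freedom. At n = 51, √(51/2) = 5.05, so the noncentrality is 0.25 for a bias of 0.05 SD and 0.76 for 0.15 SD.

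| Bias (SD) | n per group | Two-sided 5% becomes | One-sided 5%, bias in the tested direction | One-sided 5%, bias against it |
|---|---|---|---|---|
| 0.05 | 51 | 5.7% | 8.2% | 2.9% |
| 0.15 | 51 | 11.7% | 18.6% | 0.8% |
| 0.05 | 70 | 6.0% | 8.8% | 2.6% |
| 0.15 | 70 | 14.3% | 22.3% | 0.6% |

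The two-sided rate rises whichever group is older. The one-sided rate depends on the sign. More children make the distortion larger, because the bias does not shrink with n.

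**5. Equal mean ages, as expected in Group A versus Group B.**
- If ages are uniform over four months, their SD is 4/√12 = 1.155 months.
- The chance difference in mean age between arms of 70 then has SD 1.155 × √(2/70) = 0.195 months. That is 0.01-0.03 SD of score (0.195 × 0.05 to 0.195 × 0.15), and the t-test's standard error already covers it.
- Age explains (0.05 × 1.155)² = 0.3% to (0.15 × 1.155)² = 3.0% of the variance. Removing 3.0% raises power at 51 per group from 80.6% to about 81.6%, so the gain is about 1 point at most.

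**The case against.** The strongest objection is that an article leaves covariate lists to the full protocol or SAP. Age and date of birth are listed in the data set, and a mixed model could carry age. That is fair for the mixed model and the structural equation model, where age is neither named nor excluded. It does not dispose of the t-test: the method itself is fixed, and age can enter only if the test is replaced.

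Several stronger readings are tempting, but the documents do not support them.

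- *The groups do differ in age.* Nothing reports or implies this. Controls and malnourished children enter at 11-13 months and share later windows, so no mechanism for a gap is visible there. If followed children were tested exactly two years after entry, they would be 35-37 months old. That range and the reference group's 34-38 months are both centred on 36.
- *False positives in the expected direction are inflated.* Reference candidates may have aged between the 2022 census and a clinic visit as late as February 2024, although the 38-month limit caps this. If so, they would be older when tested. On scores that rise with age, this would shrink the expected advantage of treated or well-nourished children, and the one-sided rate would fall below 5%.
- *The randomised treatment comparison is biased.* Randomisation protects Group A versus Group B.
- *The mixed model codes visits as nominal years.* The text only counts three time points.

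The Data analysis plan also describes tests between and within the wasted and non-malnourished cohorts and does not spell out the reference-group contrast. That contrast is inferred from the group's stated role as an outcome reference.

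**Conclusion.** The point holds as a weakness of method, not as a demonstrated bias. The named test for univariate outcomes cannot adjust for age, and the non-randomised contrasts have no other stated protection against a difference in mean test age. The exposure is greatest for age-3 comparisons with the reference group and smaller for malnourished versus well-nourished children.

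The sizes in the working are scenarios. They rest on an assumed slope and an assumed one-month gap, and they scale in proportion to both. If mean ages turn out equal, the omission costs almost nothing. Because exact age is already recorded and validated, there is no reason to leave the matter to chance. I class this as a free improvement.

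**What to change.** In the Data analysis plan:

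- For univariate outcomes on raw scores (not age-standardised), replace the unadjusted t-test with a linear model of group plus exact age at test, computed in days from the validated date of birth. The group coefficient takes the place of the mean difference, and the 5% level and false-discovery-rate correction carry over unchanged. Scores already standardised for age need no change.
- Report the mean and SD of age at test by group and visit, so that a reader can see whether any gap exists.
- Preferably, state that exact age is the time variable in the mixed model.

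The groups share the same age windows, so the adjustment does not require extrapolation beyond the permitted ages. The cost is one covariate already in the data set, one degree of freedom and a few lines of text. No new measurement and no change in sample size are needed.
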